## Abstract

Uganda has persistently had high adolescent pregnancy prevalence; 25% for the last 10 years. This protocol presents the design of a Cluster Randomized Controlled Trial (CRCT) to investigate the effectiveness of School-Based Sexual and Reproductive Health (SBSRH) interventions on prevention of pregnancy among school girls aged 15–19 years in the Hoima District, Uganda. 18 secondary schools (clusters) will be selected using cluster sampling and allocated 1:1 into control or intervention group stratified by geographical location. 1080 (60 each cluster) participants/girls aged 15–19 years will be selected using simple random sampling. The intervention group will receive tailored SRH information, in-school medical care and referral over 12 months. The control group will receive no intervention from the research team; however, they can access alternative services elsewhere if they wish. Data will be obtained at baseline, 6 months and 12 months. The outcomes are reduction in occurrence of pregnancy, utilization of SRH services and sexual behavioral change. To our knowledge, this is the first CRCT providing combined SRH interventions for prevention of adolescent pregnancy in Uganda. If effective, it could have great potential in preventing adolescent pregnancy. Trial Registration: Pan African Clinical Trial Registry (PACTR201810882140200) Registered on 16 October 2018.

## 1. Introduction

Adolescence is a transitional phase of growth and development between childhood and adulthood, mainly referring to individuals between the age of 10 and 19 years [1]. The United Nations Children’s Fund (UNICEF) defines an adolescent pregnancy as a young girl aged 13–19 years who becomes pregnant or has had a live birth [2]. Half of the world’s population is under 25 years old and the population of young people aged between 10–25 years is estimated to be 1.8 billion with about 85% living in the developing world [2]. 49% of girls in least developed countries (LDCs) marry before they turn 18, while 10%–40% of young unmarried girls have had an unintended pregnancy, giving rise to about 14 million children worldwide who are born every year to young married and unmarried women aged 15 to 19 years [2]. In addition, the United Nation Population Fund estimates that every day in developing countries, 20,000 girls under age 18 give birth resulting into 7.3 million adolescent births a year [3].

Uganda has consistently had high rates of adolescent pregnancy at 25% for the last ten years. These rates have been coming down gradually but steadily: in 1995, it was 43%, in 2000–2001 it dropped to 31% [4] mainly because of the sexuality education program that started in schools and communities targeting young girls.

Early marriage, early initiation of sex and lack of access to reproductive health information and services are the leading drivers of adolescent pregnancy in the world [2,5,6]. A study conducted in 2018 on factors associated with teenage pregnancies among school going teenagers in eastern Uganda showed inadequate information about reproductive health with 75% of the respondents believing that the minimum age for conception is 14 years. In addition, bad peer groups, enticement with gifts and poverty were identified as the most common causes of teenage pregnancy [6]. A recent study conducted among the very young adolescents in South Western Uganda revealed that 7.6% had ever had sex yet 90% of the adolescents were not using any form of protection from HIV and pregnancy [7]. It has also been documented that the majority of adolescents usually consult their mothers and aunts for Sexual and Reproductive Health (SRH) information [8], which poses a gap in accuracy of information that is provided by the immediate relatives.

However, adolescent pregnancies may occur as a result of other factors: customs and traditions that lead to early marriage, adolescent sexual behavior, which may also be influenced by alcohol and drugs, lack of education and information about reproductive sexual health, lack of access to tools that prevent pregnancies, peer pressure to engage in sexual activity, incorrect use of contraception, sexual abuse that leads to rape, poverty, exposure to abuse, violence, family strife at home, low self-esteem and low educational ambitions or goals [9,10]. It is also important to note that adolescent pregnancy is not always a result of a deliberate choice; often, unintended pregnancy among adolescent girls is a consequence of little or no access to Adolescent Sexual and Reproductive Health (ASRH) information and services [3]. The majority of adolescent girls who become pregnant are married and/or pressured to have a child, while for others, pregnancy often results from abusive, forced or coerced sex [11]. The limited awareness on consequences of adolescent pregnancy, inaccessibility to ASRH services and social protection of the adolescent girls within the community increases the risk of becoming pregnant [3].

In sub-Saharan Africa, adolescent births are more likely to occur among poor, less educated and rural populations because of reasons including lack of access to contraception, early marriage, poor or limited access to education, cultural norms and poverty, to mention but a few [12,13]. An adolescent pregnancy poses a challenge to maternal and child survival, because pregnant adolescents and adolescent mothers are likely to be uneducated, unemployed and poor and might not seek or utilize health care services for either themselves or their newborns’ at critical times [14,15]. Thus, increased risks of maternal morbidity and mortality have been noted among pregnant and adolescents mothers [16]. This means that efforts to reduce maternal and child mortality need to focus on adolescents girls too.

Adolescent pregnancy and motherhood has detrimental socioeconomic and psychological outcomes for the young mother, her child, and her young siblings. When a girl becomes pregnant, her education may end, her job prospects diminish, she becomes more vulnerable to poverty, her health often suffers and the complications from pregnancy and childbirth are the leading cause of death among adolescent girls. The child on the other hand is likely to live in poverty, grow up without a father, become a victim of neglect or abuse, do less well at school, become involved in crime, abuse drugs and alcohol, eventually become a teenage parent themself and begin the cycle all over again [2,3].

The consequences of adolescent pregnancy include premature births, low birth weight of the newborn, high risks for medical complications such as obstructed labor, obstetric fistula, leakage of urine and/or feces and mortality [9]. Adolescent girls account for 14% of the estimated 20 million unsafe abortions performed each year, which result in approximately 68,000 deaths. This is an alarming public health problem globally and requires urgent multi-sectoral attention [9].

In 2013, there were nearly 300,000 abortions in Uganda, which is equivalent to 54 abortions per 1000 women of reproductive age, or one abortion for every 19 such women. This rate is far higher than the average rate for Eastern Africa, which is 36 abortions per 1000 women [17]. In addition, the Ministry of Health in Uganda estimated that abortions accounted for 26% of maternal mortality in 2008; this is higher than the 18% in the Eastern African region and the 13% in the world as a whole [1,17]. The Uganda Demographic Health Survey (UDHS), conducted in 2016, estimated the pregnancy-related mortality ratio to be at 368 death per 100,000 live births and adolescents 15–19 years contributing 17% of all pregnancy related mortality rate in Uganda. Additionally, 15 out of every 1000 Ugandan women of reproductive age were treated for abortion complications that year [4]. Therefore, it is paramount to pay special attention to adolescents to prevent maternal mortality due to unsafe abortions among the adolescents.

School nurses have long managed medical emergencies, helped students with chronic conditions, provided health education and immunizations and screened students’ vision and hearing; however, since the inception of these school clinics by nurses, heated debates have raged in communities across the country over whether they should provide contraceptives on-site, which clearly illustrates the role of society and resource persons in the health of the adolescents [18,19].

Several interventions have been proposed to reduce adolescent pregnancy; in particular, early education interventions have been linked to reduction in pregnancy and improvement in learning [20]. Additionally, in the absence of strong evidence that abstinence-only or abstinence-plus school-based programs affect sexual activity, the prohibition of contraceptive education in school-based pregnancy prevention programs prevents student exposure to information that has the greatest potential to decrease the pregnancy rate [21]. A recent study, conducted in Uganda on access and utilization of SRH services, found that the counseling on abstinence and other SRH issues is the most accessed and utilized service [8]. Qualitative data from a health project in Uganda shows that students can access these services while in transit to school without their parents’ knowledge and this was evidenced by the significant increment (10%) in contraceptive use among the 10–24 years during the school term compared to holiday period [22]. A study conducted in Uganda on perceptions of adolescents on SRH education by parents and other stakeholders revealed that peers and media were the main source of SRH information while mothers were perceived to provide more sexuality information to adolescents than fathers [23], this therefore indicates the need for regulation of media and the need to train more peer educators since they are the primary sources of information for adolescents.

A systematic review of 15 Randomized Controlled Trials (RCTs) conducted in developed countries on interventions for preventing unintended pregnancies among adolescents revealed that single (education) interventions were not found to be effective while combinations of interventions (educational and contraceptive access) to improve education and contraceptive access were found to reduce unintended pregnancies among adolescents. A combination of educational and contraceptive-promoting interventions appear to reduce unintended pregnancy among adolescents [24,25]. It is in this regard that this study seeks to implement a combination of education and ASRH services in a bid to reduce the occurrence of adolescent pregnancy among school girls aged 15–19 years. Key gaps that this study addressed include: (1) use of three tier interventions, i.e., education/behavioral change, services and referrals; (2) focus on school girls; (3) within an African context.

This study on the prevention of adolescent pregnancies among girls in secondary schools hinged on several theories aimed at changing behavior and primary prevention of adolescent pregnancy using school-based sexual and reproductive health services. An a priori approach will be used because the intervention proposed will be derived from existing theories without appealing to any individual experiences; the proposed model will then be implemented and tested during this research. The two main theories and approaches that will be used include: the Health Belief Model (HBM) and Trans-theoretical Model [26,27,28].

**Rationale:** This study is particularly important because it seeks to identify feasible and tested measures to promote safe sexual behavior intended to prevent adolescent pregnancy across the world. Uganda in particular has persistently had an unacceptably high adolescent pregnancy prevalence of 25% for the last 10 years compared to 16% globally [4]. This means that one in every four (25%) adolescent girls between 15 and 19 years in Uganda is pregnant or has had their first child. Despite the numerous studies that have been conducted worldwide and in Uganda on the use of school-based sexual and reproductive health services, school-based sexual and reproductive health programs are widely accepted as an approach to reducing high-risk sexual behavior among adolescents; however, these face numerous challenges in the implementation and scale-up because of the exposure of contraceptives to the school-going adolescents. In addition, incentive-based interventions that focus on keeping young people in secondary school generally reduce adolescent pregnancy; thus, there is a continued need to provide health services to adolescents using various approaches. Schools may be a good place in which to provide these services [29]. Therefore, this study focused in particular on the provision of comprehensive SRH package to adolescents in school for the reduction in risky behavior and prevention of pregnancy.

There is very limited evidence focusing on the provision of multiple interventions used in the prevention of adolescent pregnancy in both developing and developed countries. Therefore, this study therefore seeks to implement multiple interventions through a School-Based Sexual and Reproductive Health (SBSRH) model which will include both SRH information and services in selected secondary schools and will investigate the effects of providing SBSRH services on prevention of pregnancy among adolescent girls in school aged 15–19 years in the Hoima District, Uganda.

**Purpose of the study**: The purpose of the study is to determine the effect of providing School-Based Sexual and Reproductive Health information and services on the prevention of adolescent pregnancy among girls in school aged 15 to 19 years in the Hoima District, Uganda. The provision of SRH services on the school grounds was aimed at removing the barriers to access of these services among sexually active adolescents and youths so as to enable timely access to and utilization of SRH services. In addition, the study will seek to advance a suitable school-based SRH model for use in adolescent pregnancy prevention programs in Uganda and other developing countries.

**Significance of the study**: The results of the study will provide scientific evidence on the immediate, basic and underlying factors associated with adolescent pregnancies among school girls, barriers to access of SRH information and services as well as provide information on the burden of adolescent pregnancy among school girls.

Moreover, the study will provide evidence for the urgent need of combined interventions, which include SRH information, services and referral in schools. The sexual and reproductive health school model is intended to reduce barriers faced by adolescents in school in accessing accurate and timely SRH information and services in order to reduce unintended pregnancies; therefore, this study will benefit the adolescents and other stakeholders to improve access and availability of Adolescent SRH services.

The evidence from this study will be used to inform policy and planning mainly in Uganda and the African region on the effective evidence based interventions that have potential to reduce the adolescent pregnancy burden among school girls in the communities.

The study results will act as the basis for strengthening regulations and guidance on accessibility and availability of SRH services for the adolescent girls as well as provide statistics for advocacy, programming and policy development for integration of SRH services into the already existing school clinics. Implementation of the combined interventions will go a long way in contributing to the reduction of maternal and child morbidity as well as mortality by reducing unintended pregnancies among this vulnerable population.

**Aim of the study**: To develop a framework for the introduction of SRH services for adolescents in schools with the aim of improving adolescent SRH health by identifying barriers to services, surveying the current state of SRH among adolescents and assessing how adolescents respond to specific forms of SRH interventions.

## 2. Methodology

The study will use an experimental research design to assess the effect of the school-based SRH services on occurrence of the adolescent pregnancy among the school girls aged 15–19 years. The Cluster Randomized Controlled Trial (CRCT) design with qualitative and quantitative components will be used as a gold standard in conducting this impact evaluation research so as to maximize comparability between the intervention and control groups, and hence give a strong evidence of a causal relationship between the intervention and the outcome [30,31,32].

The unit of randomization will be the 18 clusters (school) and 1080 individuals (girls); therefore, the cluster (school) of the eligible girls will be randomly allocated to either the intervention (9 schools) or the control (9 schools) arms of the study.

Blinding will be done to prevent systematic biases stemming from foreknowledge of group allocations among the participants and research aim outcomes as per RCT study standards [31]. Pre-determined information, such as the research hypothesis, will be concealed from the participants, data collectors, teachers and data analysts so as to prevent biases at all levels of the research. The participants will not be made aware of the research hypothesis and will be assigned any group accordingly.

In order to avoid misleading biases, the study will use the Intent To Treat (ITT) approach for analysis. Every participant allocated to a treatment group is considered to be part of the trial. ITT will be used in an attempt to avoid potential bias and identify the true effect of the intervention.

The research will use a pre-test-post-test control group approach [33]. This is where pre-intervention (baseline) measures on the prevalence of pregnancy will be conducted to allow for explicit evaluation of the pre-to-post changes.

Qualitative data will be collected through in-depth interviews of key informants in the community and discussions with groups of adolescent boys, parents, community members and school leadership. Standard guides with open-ended questions will be used for conducting the interviews and discussions. The participants of the interviews and discussions will be purposively selected based on their role in preventing adolescent pregnancy in the community.

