#### 2.1.2. Dependent Variable: Prevention of adolescent pregnancy

Primary outcomes
(a)Incidence of pregnancy(b)Sexual and Behavior change(c)Utilization of SRH services

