#### 2.8.3. Tier Three: Referrals to off-Site Public Health Facilities

The students identified in need of advanced ASRH care such as post abortion care, antenatal care and HIV treatment will be referred to primary or tertiary public health facilities for further management. Details of the reasons for referral will be recorded and a Ministry of Health (MOH) referral form filled and given to the student. The health workers at the public health facilities nearest to the school will be sensitized about the study and possible referrals to be made and a mechanism of management of the referred cases will be developed to prevent delays and stigma associated with adolescent SRH care. The district ASRH officer will take lead in this activity for ownership but also to monitor the response of health workers during the implementation.

**Follow-up:** Follow-up of the participants will be done for 12 months and data will be collected at the start of the study, after six completed months and at the end of the study after 12 months. Data on student demographics, services received and perception towards the service and provider will collected on each clinic day to assess the level of utilization and the most sought after services.

**Control Group**: The clusters in this arm will not receive any intervention from the research team. However, the participants are free to continue accessing services from the nearby facilities as has been the case prior to the study.

**Data Collection Methods:** Quantitative data will be collected using the survey method three times that is at the start of the study (0 months), six months and at the end of the study after 12 months. Qualitative data will be collected once during the 12 months of the study through interviews and discussions with the identified stakeholders. This is intended to provide subjective and relevant information to enrich the quantitative data on adolescent pregnancy in the Hoima District.

**Data Collection Tools:** Quantitative data will be collected using a self-administered questionnaire while Qualitative data will be collected using the Key Informant Interview guide and discussions using the Focus Group Discussion guides. Additional qualitative data will be collected at other SRH service delivery point to provide a snapshot on the level of utilization of services provided; this will be done using an SRH utilization register.

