## 3. Analysis

Analysis will be done using aggregate cluster-level analysis; regression analysis using individual patient data with robust standard errors; random-effects (Res) models using individual patient data; and population averaged models using individual patient data with regression coefficients estimated using generalized estimating equations (GEEs). In this study, data exploration will be done to visualize the general feature of the data then the key analysis will be by SPSS version 20 at both cluster and individual levels. Both descriptive and inferential statistics will be analyzed allowing for the association between SBSRH service and prevention of adolescent pregnancy (occurrence of pregnancy, sexual behavioral change). The intent to treat analysis will be used to analyze patients according to their random treatment assignment, which is the intended treatment, not the treatment actually received.

Descriptive summary statistics of the clusters and individuals such as frequencies, mean, medians and standard deviations will be used to describe the characteristics of the study population on sex, age, socio-economic, education level, pregnancy status and sexual behavior, among others. Summary statistics for categorical data will be displayed in form of mean, proportion, frequencies and percentages depending on the nature of the data.

To determine the association between the dependent and independent variables, a general logistic regression model will be employed and two steps will be followed. First, each variable will be entered into a binary logistic regression model. Second, variables that are found to be significant at a p-value of 0.05 will be fitted into a multiple logistic regression model to identify independent factors of influencing occurrence of adolescent pregnancy. Variables that remain significant at a p-value of 0.05 will be further analyzed using multivariate logistic regression model and variables will be identified as independent factors influencing incidence of pregnancy and behavioral change.

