Based on the above logistical regressions, inferential statistics such as t-test and chi square test will be used to determine the similarity in the two groups using their baseline data (baseline comparison) and to determine relationships as well as associations between variables. Chi square tests will be used to test the relationships between categorical variables, while independent t-tests will be carried out to determine differences between the study groups for continuous variables with normal distribution.

Cluster level: The summary measure for each cluster (mean or proportion) will be calculated, because each cluster provides only one data point and the data will be considered to be independent while allowing standard statistical tests to be used. Multiple regressions will be used for the data summarized at the cluster level.

Individual level: During the two stage data analysis process, individual level covariates will be incorporated into the cluster analysis while accounting for the intra-cluster correlation, thus increasing the statistical power of the analysis. Statistical tests will be conducted taking into account for the clustering effect.

Qualitative data collected during the key informant interviews and focus group discussions will be transcribed and typed into a Microsoft Word computer program. These notes will be transcribed verbatim to ensure complete capturing of the responses of the study participants. Thematic analysis will be used to analyze qualitative data from key informant interviews and focus group discussions using the Atlas qualitative data analysis software version 7 (atlasti.com). Themes and sub-themes relevant to the objectives of the study will then be identified to enable development of qualitative coding and code definitions. Codes will be grouped into categories and then themes. The coded transcripts will be analyzed by running query reports and primary documents tables of codes by objective or theme and results will be used to explore the magnitude of the issues from the various focus group discussions and key informant interviews. Quotes illustrating meaning or key messages from the analysis will be selected based on the code count or how illustrative to the theme the quotes will be.

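### The 0-month survey is not fixed as a covariate for the 12-month arm comparison, so precision on sexual behaviour and service use may be lost

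*Protocol article*

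**What the plan says.** Section 2 (Methodology) adopts a pre-test/post-test control group approach, in which "pre-intervention (baseline) measures on the prevalence of pregnancy will be conducted to allow for explicit evaluation of the pre-to-post changes". The data collection text under section 2.8.3 says "Quantitative data will be collected using the survey method three times that is at the start of the study (0 months), six months", with a third round at 12 months, and "Follow-up of the participants will be done for 12 months". Participants therefore have a pre-intervention questionnaire as well as follow-up ones. Section 2.1.2 lists three primary outcomes: incidence of pregnancy, "Sexual and Behavior change", and use of services.

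Section 3 (Analysis) bears on the baseline in three places:

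- On balance between arms: "inferential statistics such as t-test and chi square test will be used to determine the similarity in the two groups using their baseline data".
- On adjustment: "individual level covariates will be incorporated into the cluster analysis while accounting for the intra-cluster correlation, thus increasing the statistical power of the analysis". The covariates are not named.
- On variable entry, in the logistic regression paragraph: "variables that are found to be significant at a p-value of 0.05 will be fitted into a multiple logistic regression model".

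The intervening factors in section 2.1.3 are age, religion, family background, education and socio-economic status. No baseline outcome is among them.

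**The concern.** A baseline measure of the outcome is often the most useful covariate a trial has, and here it is collected anyway. The two uses named for it are weak ones. A balance test can flag a chance difference between arms but does nothing to correct it. Raw change subtracts the whole baseline value, which over-corrects unless baseline and follow-up are perfectly correlated.

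The promised covariate adjustment could repair this, but nothing secures it for the baseline outcome. If the 0.05 screen were carried into the arm comparison, a prognostic baseline would enter or drop out according to its p-value in the observed data.

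With nine schools per arm, chance imbalance is not trivial. Assuming a baseline prevalence of 29%, 540 girls per arm and the plan's design effect of 1.59, the standard deviation of the baseline difference between arms is √(2 × 0.2059 × 1.59 / 540) = 0.035. That is 3.5 percentage points against a 10-point target effect. What is at stake is precision, not bias: an unadjusted comparison of randomised arms remains valid.

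**Working it through.** **Inputs from the article (sections 2.4 and 2.5):** 29% against 19%; two-sided 0.05; 80% power; ICC 0.01; 60 girls per school; nine schools per arm; 10% non-response. **Not in the article:** the baseline-to-follow-up correlation ρ. I take 0.2 to 0.7 as an assumed range.

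**The plan's own figure.** V = 0.29 × 0.71 + 0.19 × 0.81 = 0.3598. (1.96 + 0.842)² × 0.3598 / 0.10² = 282.5. Times 1 + 59 × 0.01 = 1.59 gives 449 per arm, 898 in all. Times 1.10 gives 988. 988/60 = 16.5, hence 17, then 18 schools and 1080 girls. All of this reproduces. It takes no credit for baseline adjustment, so the sample size does not depend on this point.

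**Variance factors relative to a follow-up-only comparison** (equal variances at both times):
- raw change: 2(1 − ρ), which exceeds 1 whenever ρ < 0.5;
- baseline-adjusted: 1 − ρ², which is below 2(1 − ρ) at every ρ < 1.

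In an 18-school regression the slope must itself be estimated. That multiplies the adjusted variance by about 1 + 1/14 and leaves 15 rather than 16 degrees of freedom.

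**Illustration with the pregnancy rates.** 60 less 10% is 54 girls per school, 486 per arm. The design effect is 1 + 53 × 0.01 = 1.53. Follow-up only: SE = √(0.3598 × 1.53 / 486) = 0.0337; 0.10/0.0337 = 2.97; power from the noncentral t on 16 df is 79.7%. At ρ = 0.5 the adjusted factor is 0.75 × 15/14 = 0.804, SE = 0.0302, ratio 3.31, and power on 15 df is 87.2%.

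| ρ | Follow-up only | Raw change | Adjusted |
|---|---|---|---|
| 0.2 | 79.7% | 59.7% | 78.2% |
| 0.3 | 79.7% | 65.5% | 80.3% |
| 0.5 | 79.7% | 79.7% | 87.2% |
| 0.7 | 79.7% | 94.9% | 96.3% |

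A simulation of school means (4000 runs, same ρ at girl and school level) agrees, in the same column order: 80.4/60.8/78.5 at ρ = 0.2, 79.6/65.8/79.7 at 0.3, 78.5/79.9/86.6 at 0.5 and 79.3/95.2/96.5 at 0.7.

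**Incident pregnancy.** A girl's own pregnancy status at 0 months bears on whether she is at risk, so it is not an ordinary covariate. That leaves the school's baseline prevalence. If the girl-level correlation is zero (assumption), the correlation of school means is (m × ICC × school-level correlation) / (1 + (m − 1) × ICC). At 60 girls and ICC 0.01 its ceiling is 0.6/1.59 = 0.38. School-level correlations of 0.3, 0.5, 0.8 and 1.0 give 0.11, 0.19, 0.30 and 0.38. Adjusted power is then 79.7, 80.6, 82.9 and 85.0%, against 82.2% unadjusted with 60 girls per school. The change runs from about −2.5 to +3 points.

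**The case against.** The strongest reply is that the plan already intends to adjust. Section 3 says individual-level covariates will be used to gain power, and a condensed article may leave their names to a fuller document. That stands against any claim that adjustment is absent. It does not dispose of the point, because the article is not merely silent: it states what the baseline is for and gives one rule for variable entry, and neither secures the baseline outcome as a covariate.

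Three stronger readings are tempting and should not be drawn.

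- A reader might infer that the plan commits to a raw change analysis. It does not. The sentence in section 2 is general design text, the methods listed in section 3 include no change-score estimator, and the behaviour outcome's title names an outcome, not an analysis. The raw-change column above shows what such an analysis would cost, not what the plan has fixed.
- A reader might infer that the 0.05 screen governs the arm comparison. It is written for finding factors that influence pregnancy. The covariate sentence carries no such screen, and only a loose reading joins the two.
- A reader might infer that the trial gives up 8 to 10 points of power. The normal approximation at ρ = 0.5 does give 86.7% against 94.4% with 540 girls per arm (80.0% against 89.9% with 449). But 0.5 is an assumption, and for pregnancy at ICC 0.01 the usable correlation cannot exceed about 0.38 under the assumption above.

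It also stands that no rates, scales or correlations are given for sexual behaviour or service use, so their loss is illustrated and not demonstrated.

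**Conclusion.** The point holds as one of efficiency and prespecification, not validity. The baseline outcome is measured and given two weak named uses, and nothing guarantees it a place in the arm comparison. Always adjusting for it is a better method that needs no new data.

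The benefit lies mainly in sexual behaviour and service use. On borrowed pregnancy rates, it is about nil at ρ = 0.3 and about 7 points at ρ = 0.5 against follow-up only. Against raw change, should that be used, it is about 15 and 7 points. For incident pregnancy the effect is small and of either sign at the plan's ICC. At an ICC of 0.05, inside the range the article cites, it would be about 3 points at a school-level correlation of 0.5 and about 15 at 0.8. Confidence is medium, because every figure rests on an assumed correlation.

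**What to change.** In section 3, state that:

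- the arms are compared on the 12-month values of sexual behaviour and service use, always adjusted for the girl's own 0-month value and the school's baseline mean, whatever their p-values;
- in the cluster-level analysis of these outcomes, the school's 12-month summary is regressed on arm and the school's 0-month summary;
- covariates for the arm comparison are not chosen by significance, and the 0.05 screen is kept to the risk-factor model.

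In section 2, say that raw pre-to-post change is reported descriptively. For incident pregnancy, adjustment for school baseline prevalence is optional; decide it in advance.

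The change is wording only: no new data, visits or participants. The cost is one degree of freedom and an estimated slope in the 18-school regression. That is about 1.5 points of power at ρ = 0.2, rising to about 3 at ρ = 0 (76.5% against 79.7%). A logistic model that includes the baseline estimates a conditional odds ratio, so an adjusted risk difference should be reported beside it.
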